#### Secondary outcome measures

Degree of fatigue measured using the Functional Assessment of Chronic Illness Therapy-Fatigue questionnaire (FACIT-Fatigue).Radiological response to treatment (Response Evaluation Criteria In Solid Tumors, RECIST) [39].Functional capacity (6-Minute Walk Test; cardiorespiratory fitness test measured using a cycle ergometer submaximal exercise test).Muscle strength (hand-held dynamometry and 5-times sit-to-stand test).Progression-free and overall survival.

##### Costs

The costs will be assessed from the perspective of the programme. That is, we will only include healthcare costs related to the intervention, in line with the recommendations of the National Institute for Health and Clinical Excellence (NICE) in the UK. We will use a bottom-up approach to estimate costs. This methodology consists of recording the resources used by each centre and converting these into currency units. The costs will be classified as: 1) time dedicated to the programme by healthcare staff involved, namely, nurses; 2) consumables; and 3) structural costs.

Predictive (or confounding) variables.

Age, sex, type of cancer (breast, gastrointestinal or lung), chemotherapy regimen, ECOG PS, and smoking status.

### Adverse events

An external committee will review and compare all non-serious adverse events, while researchers will be obliged to report any serious adverse events to the research unit by fax. A coordination committee with access to all the information it needs will undertake preliminary analyses of the data to monitor the safety of the programme. This committee will be composed of individuals that are independent of the organisation responsible for the study management and members of the research team including the study coordinator, all blind to patient allocation. In addition to serving on the committee, the coordinator will phone the participating health centres daily, to check on the progress of the study, report weekly on this progress to the principal investigator of the study, produce a monthly report with the study data, and make recommendations to the study management team.

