## Methods/design

### Study design

This is a parallel-group randomised controlled clinical trial in patients with breast, gastrointestinal or non-small cell lung cancer at stage IV of the disease. The treatment common to both groups will be the usual care for cancer, namely, optimized usual drug therapies and strengthening of self-care. The intervention group will also receive an intervention based on a supervised exercise programme led by nurses combined with education on healthy living. The patients included in the study will pass through two successive phases: a “treatment optimization phase” and a “phase for follow-up and assessment of results”. Patients are to be followed-up for 1 year, with four blind assessments: at baseline, and 2, 6 and 12 months later (Figure 1).

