### Protocol for the control group

Patients in the control group will all receive the usual treatment for the type of cancer they have been diagnosed with (e.g., platinum-based chemotherapy for non-small cell lung cancer), following standard oncological criteria. They will be assessed before, during and after chemotherapy in accordance with the established protocol.

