#### Phase 1 (8 weeks, 3 sessions/week)

For the first 2 months, patients will follow a progressive exercise programme consisting of 24 sessions, the intensity being lower at the beginning and increasing in the second month (Figure 2). Two of the sessions each week will take place under the supervision of the nurse in the laboratory, while the third session is to be carried out independently in the area around the health centre, with the aim of promoting patient independence, and for this, patients are to wear a heart rate monitor pre-programmed by the nurse. Each laboratory session will include health education, as well as aerobic exercise and muscle strength exercises.

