#### Aerobic exercise

In each session, the intensity of the exercise is adapted to the physical condition of patient. The activity will be monitored using the Borg scale to rate the patient’s perceived exertion before and after each session and by watching for the appearance of symptoms. During the first month, patients will perform continuous aerobic exercise at a constant intensity equivalent to 60-70% of their heart rate reserve (HRR). In the second month, the intensity of the exercise will be increased, patients performing aerobic interval exercise, alternating 5-minute periods of very high intensity at 75-90% of their HRR with 2-minute periods of active resting at 40% of their HRR. This aerobic exercise is to be carried out before strength exercises to ensure cardiovascular and muscular warm-up.

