Regardless of whether the exercise turns out to be effective, we can be confident that the programme is safe and does not represent any additional risk for cancer patients. Specifically, other similar studies have reported no adverse effects associated with exercise [32,42,43].

This study offers the possibility of assessing the experience of patients with an exercise programme and demonstrates well-coordinated work of the oncology and primary care units in tertiary prevention. Indeed, given our positive experience, we are already considering developing this type of physical exercise programme for individuals with other chronic disorders.

In summary, our hypothesis is that a programme of physical exercise coordinated between the oncology and primary care units, supervised at health centres by nurses to safeguard patient safety but which can be can be continued in the community setting, and common for all types of cancer while tailored to meet individual patient needs, will be effective in improving the quality of life of patients with cancer as well as being cost-effective.

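### The planned comparison of all non-serious adverse events is at risk of detection bias, because only the intervention arm has 16 nurse-supervised sessions at which symptoms are watched for

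*Protocol article*

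**What the plan says.** The protocol article (Adverse events) sets the rule for non-serious events in one clause: "An external committee will review and compare all non-serious adverse events". It does not name what is compared with what, or how these events reach the committee. Serious events have a separate reporting route.

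For the intervention arm, the section on Phase 1 states that "patients will follow a progressive exercise programme consisting of 24 sessions" and that "Two of the sessions each week will take place under the supervision of the nurse in the laboratory". The third weekly session is done alone with a heart rate monitor. The Aerobic exercise section adds that the Borg scale is used to "rate the patient’s perceived exertion before and after each session and by watching for the appearance of symptoms".

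For the control arm, the article says "They will be assessed before, during and after chemotherapy in accordance with the established protocol". Under Study design, "The treatment common to both groups will be the usual care for cancer", and all patients have the same four trial assessments, at entry and at months 2, 6 and 12. No contact in the control arm corresponds to the supervised sessions.

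**The concern.** A comparison of adverse event counts is fair only if an event has about the same chance of being noticed and recorded in each arm. The rule here takes in every non-serious event, whatever its source, while the design places a nurse beside one arm's patients twice a week for two months. Mild, short-lived symptoms are the events most likely to be caught at such a session and missed when the next contact is weeks away. The article's Background describes fatigue and dyspnoea as part of the disease and its treatment, so such symptoms are to be expected in both arms.

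What is at stake is how an excess in the exercise arm would be read. It could come from the exercise or from closer observation, and a pooled count would not show which. A real excess could be explained away as surveillance, and an artefact could be taken for harm.

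**Working it through.** **1. Extra contacts (inputs from the Phase 1 section).**
- All sessions: 8 weeks × 3 per week = 24, which reproduces the article's figure.
- Supervised sessions: 8 × 2 = 16 in the intervention arm, against 0 in the control arm.

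**2. Contacts common to both arms (Study design; Protocol for the control group).** The four trial assessments and the oncology care around chemotherapy apply to both arms. They raise capture in both arms, but they do not remove the difference of 16.

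**3. How the difference acts.** Let *c* be the share of non-serious events captured through the shared contacts. Let *s* be the share of the remaining events that are captured at supervised sessions and passed to the committee.
- Capture in controls: *c*
- Capture in the intervention arm: *c* + (1 − *c*)*s*
- Apparent rate ratio when the true rates are equal: [*c* + (1 − *c*)*s*] / *c* = 1 + *s*(1 − *c*)/*c*

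The ratio is 1 only if *s* = 0 (session observations never become adverse event records) or *c* = 1 (the shared contacts miss nothing). Otherwise it exceeds 1. In this model the bias runs one way, towards more events in the exercise arm.

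**4. Illustration on assumed values.** The article gives no adverse event rate and no capture rate. All capture figures below are assumptions, with intervention-arm capture held at 90%.

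| Capture, intervention | Capture, control | Apparent rate ratio |
|---|---|---|
| 90% | 90% | 0.90/0.90 = 1.00 |
| 90% | 70% | 0.90/0.70 = 1.29 |
| 90% | 50% | 0.90/0.50 = 1.80 |

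With 33 patients per arm (Sample size section) and an assumed true mean of 1 event per patient, the recorded counts would be 33 × 0.90 = 29.7 in the intervention arm. In controls they would be 33 × 0.70 = 23.1 or 33 × 0.50 = 16.5.

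**5. Could such a gap look like a finding?** Under a Poisson model with the same assumed mean of 1, the proportion of patients with at least one recorded event is 1 − exp(−capture): 0.593 at 90%, 0.503 at 70% and 0.393 at 50%. With 33 per arm, a test of two proportions at a nominal 5% would be significant about 11% of the time for 90% against 70%, and about 37% of the time for 90% against 50%, with no true difference. The Statistical analysis section mentions no adverse event test, so these figures only show scale.

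**The case against.** The strongest reply is that the article is silent rather than wrong. It does not state that the comparison is between arms. It describes symptom watching as part of monitoring the exercise and nowhere says that what is seen is logged as an adverse event. It refers to fieldwork manuals and registration forms that are not shown and may set out a common way of eliciting events. This stands as far as certainty goes: a reader might infer that the comparison is biased, and the document supports only that it is at risk. It does not remove the point, because the rule that is stated covers all non-serious events and so, on its face, admits whatever is noted at sessions.

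A reader might also infer that controls are unobserved. They are not: they have the shared assessments and oncology care. What they lack is a counterpart to the 16 sessions.

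A third tempting inference is that the comparison can support no conclusion in either direction. That goes too far. The expected bias inflates events in the exercise arm, so finding no excess despite closer observation would be reassuring. The EORTC QLQ-C30, completed by both arms on the same schedule, also covers fatigue, pain, nausea and vomiting, and dyspnoea. That is a partial check, limited by its 7-day recall.

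Blinding does not answer the concern. The statement about blinding is attached to the coordination committee, not clearly to the external one, and a blinded review cannot recover control events that were never recorded.

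Lastly, the Discussion says "we can be confident that the programme is safe and does not represent any additional risk for cancer patients". It is tempting to treat this as resting on the planned comparison. It does not: it is argued from similar published studies, and is a separate matter that neither strengthens nor weakens this point.

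**Conclusion.** The concern holds as a risk of detection bias, conditional on two readings: that the comparison is between arms, and that session-observed symptoms can enter it. The first is the natural reading in a two-arm trial. The second follows from the scope of the stated rule but is not written. The imbalance of 16 supervised sessions against none is certain. The resulting bias cannot be sized from the document; ratios of about 1.3 to 1.8 arise only on the assumed capture rates, and equal capture gives 1.0.

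The consequence is confined to the reading of an apparent excess of non-serious events in the exercise arm. Non-serious events are not listed among the primary or secondary outcomes, so the quality-of-life result is untouched. The point still merits a correction, because the remedy is cheap and gives a comparison that an excess could be judged by.

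**What to change.** In the Adverse events section, replace the comparison of all non-serious events with a rule of this kind:

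*Non-serious adverse events will be compared between arms only if they were elicited in the same way in both: by the same event questions at the 2-, 6- and 12-month assessments, or from the oncology record reviewed by the same procedure in each arm. Events noted during exercise sessions will be reported separately, for the intervention arm only, as a rate per session.*

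The denominator for that rate would be the sessions attended. For supervised sessions the maximum is 33 × 16 = 528.

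The cost is a short set of event questions at visits already planned, and the change of wording. No visits are added. The downside is that fewer mild events enter the formal comparison, although those seen at sessions remain visible in the separate report.

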### Follow-up period

One year from the beginning of the intervention.

### Sample size

We estimate that we need to analyse 26 patients per group to detect a difference of 20 points in the global scales and subscales of the EORTC QLQ-C30 as significant, a difference considered to be important from the patient point of view (level of significance, 0.05; power, 0.80 and standard deviation, 25). For this reason, we will include 33 patients per group, that is, a total of 66, allowing for a loss to follow-up of 20%. Given that in the pilot 66% of candidates signed the informed consent form, we need to invite a total of 100 patients to participate.

### Statistical analysis

The primary outcome variable has been found to have a normal distribution in previous studies; for variables that are non-normally distributed, non-parametric tests will be used and models built suitable for their type of distribution. Analyses will be conducted on an intention-to-treat basis, and changes between groups compared at each time point of the follow-up, by analysis of covariance adjusting for baseline levels. The effect attributable to the intervention will be estimated by assessing the differences in improvement in the groups, with 95% confidence intervals. Stratified analysis and statistical models, linear for continuous outcome variables and logistic for dichotomous variables (quantitative categorized variables), will be used to adjust these comparisons for potential confounding factors. To assess the change overall over the 1-year follow-up, we will estimate the effect of time on three repeated measures in each subject, using mixed linear regression models, fixed effect models (time, intervention, interaction between time and intervention) and random effect models (specific effect of each subject and each centre on the baseline and on the effect of time). These models will take into account the longitudinal nature of the data from three repeated measurements in each patient and will be extended to adjust for the putative predictive (or confounding) variables.

Estimates will be made of the incremental cost-effectiveness and cost-utility ratios, dividing the increase in cost between the groups by the increases in effectiveness and utility, respectively. Confidence intervals will be calculated for these ratios using random sampling techniques (bootstrapping). Sensitivity analysis will be performed, changing the assumptions of the analysis. All analyses will be carried out using the SAS statistical package.

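### Bootstrap confidence intervals are planned for the cost-effectiveness ratios themselves, and these have no meaningful finite form if the interval for the effect includes zero

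*Protocol article*

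**What the plan says.** The Statistical analysis section defines the cost-effectiveness and cost-utility ratios by "dividing the increase in cost between the groups by the increases in effectiveness and utility, respectively". On their uncertainty it says: "Confidence intervals will be calculated for these ratios using random sampling techniques (bootstrapping". It adds a sensitivity analysis that varies the assumptions, without saying which. It names no method for a denominator that may be zero or change sign.

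The Costs section limits the numerator: "we will only include healthcare costs related to the intervention". It lists nurse time, consumables and structural costs.

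The Sample size section gives the only precision figures. The trial is sized "to detect a difference of 20 points in the global scales and subscales of the EORTC QLQ-C30 as significant", with "level of significance, 0.05; power, 0.80 and standard deviation, 25", so that "we need to analyse 26 patients per group". The Limitations section concedes limited power for differences below 10 points, which it says patients might still find relevant. It also says that about 100 per group had been thought necessary for a difference of that kind.

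Efficiency stands beside efficacy in the Aim, and the closing hypothesis in the Discussion is that the programme will be cost-effective.

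**The concern.** A ratio is a poor quantity for a confidence interval when its denominator can be zero. Controls do not receive the programme, so with programme-only costs the incremental cost is essentially always positive. A small positive effect then gives a very large positive ratio, and a small negative effect gives a very large negative one. The two lie at opposite ends of the number line although they are neighbours in meaning.

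If the effect interval runs from a negative lower limit to a positive upper limit, the compatible ratios are everything above one positive value and everything below one negative value. No single finite interval describes that set. Sorting bootstrap ratios and reading off the 2.5th and 97.5th percentiles nevertheless returns two finite numbers. The interval between them contains small positive ratios that would need a larger benefit than the data support. It leaves out the extreme ratios that correspond to almost no benefit.

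This interval is the only inference described for the economic question.

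**Working it through.** **Inputs.** From Sample size: difference 20 points, SD 25, significance level 0.05 (two-sided assumed), power 0.80, 26 analysed per group. From Costs: programme costs only. Assumed, because the article does not say: effectiveness means QLQ-C30 points; the baseline correlation r is 0, 0.5 or 0.7; the cost figures below are illustrative, in arbitrary units.

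**1. The plan's own figure.** n per group = 2 × (1.96 + 0.84)² × 25² / 20² = 24.5, so 25 by the normal approximation. The t-test version gives 25.5, so 26, as stated. Then 26 / 0.80 = 32.5, so 33 per group and 66 in total, as stated. For 10 points the same formula gives 99, in line with the 100 per group in Limitations. The SD of 25 therefore fits both of the article's sample sizes.

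**2. Precision of the denominator.** SE = 25 × √(2/26) = 6.93. The 95% half-width is 1.96 × 6.93 = 13.6 points (13.9 with t on 50 degrees of freedom). An unadjusted observed effect below about 14 points leaves zero inside the interval. With baseline adjustment, SE = 6.93 × √(1 − r²), which is 6.00 at r = 0.5 and 4.95 at r = 0.7.

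**3. How often the effect interval includes zero.** By the normal approximation, P = Φ(1.96 − d/SE) − Φ(−1.96 − d/SE) for true effect d. The t-based value is in brackets.

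| True effect | r = 0 | r = 0.5 | r = 0.7 |
|---|---|---|---|
| 5 | 89% (89%) | 87% (87%) | 83% (83%) |
| 10 | 70% (71%) | 62% (63%) | 48% (49%) |
| 15 | 42% (44%) | 30% (31%) | 14% (16%) |
| 20 | 18% (19%) | 8.5% (9.6%) | 1.9% (2.3%) |

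**4. Share of replicates with a negative denominator.** This is about Φ(−observed effect / SE). At 10 points observed, Φ(−10/6.93) = 7.5%; at 5 points, Φ(−5/6.93) = 23.5%. With r = 0.5 to 0.7, the 10-point figure falls to 4.8% and 2.2%.

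**5. What percentile limits would look like.** Take an incremental cost fixed at 500 units and an observed effect of 10 points with SE 6.93.
- The effect interval is 10 ± 13.6, that is −3.6 to 23.6.
- The compatible ratios are above 500/23.6 = 21 or below 500/(−3.6) = −139.
- The lower percentile limit −k solves P(−500/k < effect < 0) = 0.025, giving about −349. The upper limit k solves P(0 < effect < 500/k) = 0.025, giving about 455.
- The interval −349 to 455 contains every ratio from 0 to 21, which needs an effect above 23.6. It excludes only effects between 500/(−349) = −1.4 and 500/455 = 1.1, the near-null ones.

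**6. Simulation.** 1,000 trials were run with 1,000 resamples each, 26 per arm, SD 25, and an assumed incremental cost with mean 500 and SD 100. Denominators of both signs fell in the central 95% of resamples in 87%, 67%, 42% and 16% of trials at true effects of 5, 10, 15 and 20 points. At 10 points (true ratio 50) the median percentile limits were −307 and 426. At 20 points (true ratio 25) they were 14 and 76, an ordinary interval.

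**The case against.** A reader might infer that the trial's low precision makes a near-zero effect likely, so that its whole efficiency result would be uninterpretable. The documents do not support that. Low precision widens the interval; it does not move the effect towards zero. At the 20 points for which the trial is sized, the problem is the exception. Limitations concedes weak power below 10 points but does not say such effects are expected. Even when the ratio interval fails, the point ratio, the replicates and the separately planned 95% interval for the effect remain readable.

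Further points stand in part:
- The article says bootstrapping and does not name the percentile method. A fuller analysis plan may order the replicates sensibly or add a cost-effectiveness plane. But the article does commit to intervals on the ratios, and no bootstrap variant gives a meaningful finite interval when the denominator spans zero.
- With a positive cost difference, a negative ratio always means dominated, so the replicates can be ranked with those last. This removes the ambiguity of sign. The worst limit is then still not a finite ratio.
- Naive limits with a negative lower end look odd and should alert a careful reader. A careless one could take the negative limit for a saving.
- The simulated percentile intervals covered the true ratio in 96% to 98% of trials at effects of 5 to 20 points. The fault is therefore not under-coverage at those effects. It lies in which ratios the interval admits and which it omits.
- The planned analysis of covariance would improve precision if the denominator is baseline-adjusted, which is why the range over r is shown.

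**Conclusion.** The concern holds conditionally. The article fixes intervals on the ratios, and these have no meaningful finite form in any trial whose effect interval includes zero. On QLQ-C30 points with 26 per arm and SD 25, that is about 19% of trials at the design effect of 20 points, and about 2% to 9% (normal approximation) with a baseline correlation of 0.5 to 0.7. At 10 points it is about 71%, and about 48% to 62% with that correlation.

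These figures rest on a two-sided 5% level, on QLQ-C30 points as the effectiveness measure, and on a baseline correlation that the article does not give. They do not extend to the cost-utility ratio, for which there is neither an SD nor an expected effect. The primary outcome, sample size and data collection are unaffected. This is a defect in a secondary analysis, worth correcting because efficiency is part of the stated aim and the correction is cheap.

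**What to change.** Report the cost-effectiveness and cost-utility ratios as point estimates only. Base inference on incremental net benefit, λ × (difference in effect) − (difference in cost), over a stated range of willingness-to-pay λ, with bootstrap 95% confidence intervals. Net benefit has no denominator, so its interval is well behaved whether or not the effect is near zero. Show the same replicates on the cost-effectiveness plane and as an acceptability curve. State which outcome is the measure of effectiveness and whether its difference is baseline-adjusted.

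The cost is a change of wording in the analysis plan and slightly more analysis work. A willingness-to-pay range must be chosen and stated, both per unit of effectiveness and per unit of utility. No extra patients or data are needed.
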